## Abstract

**Background:**

Simulation-based medical education (SBME) is a cornerstone for procedural skill training in residency education. Multiple studies have concluded that SBME is highly effective, superior to traditional clinical education, and translates to improved patient outcomes. Additionally it is widely accepted that mastery learning, which comprises deliberate practice, is essential for expert level performance for routine skills; however, given that highly structured practice is more time and resource-intensive, it is important to assess its value for the acquisition of rarely performed technical skills. The bougie-assisted cricothyroidotomy (BAC), a rarely performed, lifesaving procedure, is an ideal skill for evaluating the utility of highly structured practice as it is relevant across many acute care specialties and rare – making it unlikely for learners to have had significant previous training or clinical experience. The purpose of this study is to compare a modified mastery learning approach with deliberate practice versus self-guided practice on technical skill performance using a bougie-assisted cricothyroidotomy model.

**Methods:**

A multi-centre, randomized study will be conducted at four Canadian and one American residency programs with 160 residents assigned to either mastery learning and deliberate practice (ML + DP), or self-guided practice for BAC. Skill performance, using a global rating scale, will be assessed before, immediately after practice, and 6 months later. The two groups will be compared to assess whether the type of practice impacts performance and skill retention.

**Discussion:**

Mastery learning coupled with deliberate practice provides systematic and focused feedback during skill acquisition. However, it is resource-intensive and its efficacy is not fully defined. This multi-centre study will provide generalizable data about the utility of highly structured practice for technical skill acquisition of a rare, lifesaving procedure within postgraduate medical education. Study findings will guide educators in the selection of an optimal training strategy, addressing both short and long term performance.

## Background

There is substantial evidence that SBME is a superior training technique compared to traditional didactic methods for technical skill acquisition [1, 2]. As both technology and patient care become increasingly complex, simulation-based medical education (SBME) provides a feasible alternative allowing trainees to practice without harming patients [3]. Unfortunately, SBME is a resource intensive approach to medical training, requiring careful alignment of education and practice design principles with the intended outcomes. For example, there is growing evidence that deliberate practice and mastery learning approaches to training for procedural skills can ensure expert level performance, particularly for routine procedures [4–7]. Applying this structured approach, learners can transition as outlined in the “Dreyfus model” along a continuum of five stages: novice, advanced beginner, competent, proficient and expert [4]. Highly structured practice requires a substantial commitment of time and instructional resources [8]. Identifying the most effective and evidence-based SBME methods for rare procedures is a critical task for educators in acute care medicine [9, 10].

### Deliberate practice and mastery learning (DP + ML)

Deliberate practice (DP) is an instructional method widely regarded as the mainstay for expert skill acquisition [11–13]. First described by Ericsson and his colleagues, this method refers to engagement in structured activities with the goal to improve performance in a domain, through an iterative cycle of practice, feedback, and successive refinement [14]. It is based on 4 key components [11]:Motivated learnersWell-defined goals for improvementAmple opportunity to practice through repetitionDuring practice, focused feedback is provided with skill adjustments made accordingly

Deliberate practice is often coupled with the mastery learning (ML) model, where tasks are broken into a series of smaller and progressively more complex microskills [15]. Learners advance through each of the tasks by applying skills they have acquired during preceding steps [16] (Fig. 1). Deliberate practice and masterly learning (DP + ML) improves performance across a variety of disciplines including sports and music and there is growing evidence of its effectiveness within medical education [2, 12, 17].

**Fig. 1 Fig1:**
[figure not shown]
Deliberate practice model. Deliberate practice occurs over time with repeated feedback and refinement of microskills, combined together resulting in improved task completion

Some authors suggest that simulation training using DP + ML results in superior outcomes compared to other methods of simulation-based practice [2]. An alternative to DP + ML is self-guided practice (also referred to as self-directed or self-regulated) whereby “*individuals take the initiative, with or without the help of others in diagnosing their learning needs, formulating learning goals, identifying human and material resources for learning, choosing and implementing appropriate learning strategies, and evaluating learning outcomes*” [18]. The few studies that compare DP with self-guided practice yielded mixed results while also limited by both small sample sizes and generalizability of a single institution setting [8, 19].

An important confounding factor that may explain these discrepant results is the variability in how DP is applied during SBME. Deliberate practice is often described in the context of sustained investment in practice over long periods of time in order to attain expert status [9]. In medical training, this can be difficult given the wide breadth of skills and knowledge that are required, especially when it comes to rarely performed procedures. While most clinical educators adhere to the key components of Ericsson’s criteria, in real practice, training is condensed over a shorter time-frame. The goal of the current study therefore is to explore the application of DP in a realistic context in order to understand how it is best optimized in curricular design, particularly for the acquisition of a rarely performed technical skill in the emergency medicine setting. Our study design incorporates several metrics of performance including a global rating scale and chronometry measured both immediately after and 6–12 months following skill instruction.

### Chronometry

Chronometry, the measurement of time, is an important metric for time sensitive procedures yet it remains uncommonly applied within technical skill training curricula [20]. However, introducing procedural time-based measurements can further improve deliberate practice by facilitating overlearning (going beyond the minimal level of competence required), increasing the challenge level, and providing additional feedback which can enhance a learner’s self-assessment and increase motivation [20].

### Retention

A key aspect of procedural skill acquisition is skill retention. Medical trainees are expected to demonstrate competence in performing a wide array of procedures, despite having limited exposure to practice opportunities [21]. Acute care physicians face the additional challenge of performing these procedures with little to no warning in stressful situations with unstable patients.

Several studies have looked at SBME to improve skill retention yielding variable results. Skill decay ranges from 2 weeks to 14 months for procedures such as ACLS, shoulder dystocia and cricothyroidotomy skills, with the most common retention interval being 6–12 months [22–25]. These differences are perhaps unsurprising, given that there are a number of different factors that influence retention including degree of overlearning, performance conditions during retention evaluation, task characteristics, and unmeasured individual differences [26–30]. While it appears that 6–12 months is a reasonable timeframe to expect for skill retention, there is uncertainty regarding the training approach best suited to optimize skill performance over time.

### Bougie-assisted cricothyroidotomy

The cricothyroidotomy is a life-saving procedure performed as a final option in all emergency airway algorithms [31, 32]. It represents an ideal prototype to evaluate the utility of DP + ML in skill acquisition and retention as it is rare, time-sensitive, and relevant across most acute care, hospital-based specialties [31, 33–36]. Furthermore, the recent introduction of a novel technique—the bougie-assisted cricothyroidotomy (BAC)—offers additional opportunity as residents are unlikely to have previous training or experience.

#### Justification/summary

Large scale, multi-centre, comparative effectiveness studies of SBME methods are needed to better define optimal simulation teaching strategies. This study will compare DP + ML with self-guided practice on the acquisition and retention of a rarely performed skill –bougie assisted cricothyroidotomy. To our knowledge, this is the first multi-centre, randomized study to evaluate the role of DP + ML on skill acquisition and retention.

## Methods

### Aim/objective

The objectives of this study are to:Compare two instructional techniques on the skill performance of a bougie-assisted cricothyroidotomy immediately and after 6–12 months after trainingEvaluate participant attitudes and preferences following two instructional techniques and practice

### Study design and setting

This is a multi-centre, blinded, randomized study (Fig. 2). The study will take place at five emergency medicine (EM) residency programs across North America (4 Canadian- and 1 US-based centres). All EM residents PGY1–5 are eligible and will be invited to participate. Written consent will be obtained from all study participants. There are no exclusion criteria. We received research ethics board approval from all participating institutions.

**Fig. 2 Fig2:**
[figure not shown]
Study design

### Instructional methods

Residents at each study site will be assigned to receive either DP + ML, or self-guided practice using a computer-generated randomization process. Participants will be blinded to the study group assignments. For practical purposes, we will cluster 4–6 participants with 1 instructor who will facilitate the training using one of the two instructional methods. This group size aligns with recommendations from surgical education literature for procedural skill training that demonstrates the optimal trainee:instructor ratio for procedural skills training [37]. All instructors are board certified emergency physicians with expertise in procedural skill training. Prior to the session, each instructor will receive an introduction to the task trainer, a briefing on how to conduct the training and a standardized approach to BAC performance. The instructors assigned to the DP + ML session will also receive an introduction to the BAC checklist and explicit instructions to facilitate mastery learning followed by deliberate practice [38]. The instructors assigned to the self-guided practice session will be told explicitly that they can only provide feedback following a participant request. They will be instructed by the study investigators on the necessary steps for BAC performance.

Both groups will receive an introductory lecture to surgical airway performance and a demo of the BAC on the task trainer by the session instructor. Participants will then complete a pre-training survey assessing self-confidence and prior cricothyroidotomy experience, followed by a video-recorded performance of a BAC using an upper body task trainer (head and neck from a Laerdal SimMan) to assess baseline performance before training begins.

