### Primary outcome

The primary outcome is the difference in skill performance of BAC between the two groups at post-training, assessed using a previously validated 7-point global rating scale (GRS) [22, 39]. Video recordings will be scored by three independent airway experts (2 Royal College certified emergency physicians, 1 staff anesthesiologist) trained in BAC. All reviewers will receive training from study investigators followed by practice video review to ensure scoring standardization. All reviewers will be blinded to the subjects’ identities and group allocation.

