### Statistical analysis

The survey data will be analyzed using descriptive statistics. The primary outcome (GRS) score will be evaluated using a repeated measures ANOVA with between subject factor of instruction (DP + ML or SG group) with one within subject factor of assessment repeated 3 times (pre, post, and retention). SPSS software (SPSS Inc. 18.0, Chicago IL) will be used for data analysis. 2-sided *P* < 0.05 is considered statistically significant for the primary outcome. Interrater reliability (IRR) for the reviewers’ scores will be analyzed using an intraclass correlation, after reviewing the same 20 videos. If a target IRR of ≥0.7 is achieved, the rest of the videos will be scored by one reviewer. Confidence ratings will be compared with GRS at pre-training, post-training and retention using Spearman’s correlations.

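### The primary model omits site and training level although residents are assigned within five sites and span PGY1–5, so the post-training comparison loses some precision but is not biased

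*Protocol article*

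**What the plan says.** - **Assignment** (Protocol article, Instructional methods): "Residents at each study site will be assigned to receive either DP + ML, or self-guided practice using a computer-generated randomization process". No stratification by training level is stated.
- **Sites** (Study design and setting): "The study will take place at five emergency medicine (EM) residency programs across North America (4 Canadian- and 1 US-based centres").
- **Population** (same section): "All EM residents PGY1–5 are eligible and will be invited to participate". There are no exclusion criteria.
- **Baseline data** (Instructional methods): participants complete a "pre-training survey assessing self-confidence and prior cricothyroidotomy experience" and then a recorded attempt before practice, which gives a pre-training GRS.
- **Primary outcome** (Primary outcome): "The primary outcome is the difference in skill performance of BAC between the two groups at post-training".
- **Primary model** (Statistical analysis): a "repeated measures ANOVA with between subject factor of instruction (DP + ML or SG group"). The only other term named is assessment time, at three levels: before training, straight after it, and at the retention visit.

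Site, PGY level and prior experience do not appear as factor, covariate or stratum in the Sample size determination or Statistical analysis sections. The article also does not say which term of the ANOVA tests the post-training difference.

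**The concern.** When arms are formed within each site, differences between sites largely drop out of the arm contrast. A model without a site term still counts those differences as error, so its standard error is larger than the design warrants. Training level is different. It is not said to be balanced by design, so its variance adds real noise to the estimate, and a pre-specified covariate can remove part of that noise.

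What is at stake is precision: wider intervals and less power than 160 residents could give. A second, smaller matter is that fixing the adjusted model in advance prevents a later choice between adjusted and unadjusted results.

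**Working it through.** **1. The plan's own figure.** The article claims 80% power with 80 per group for a difference of 1.3 GRS points at two-sided α = 0.05. No SD is stated, so the figure can only be solved backwards: SD = 1.3 / [(1.960 + 0.842) × √(2/80)] = 1.3 / 0.443 = 2.93, a standardised effect of 0.44. The power figures below depend only on the 80% starting point, not on this SD.

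**2. Which tests are affected.** A repeated measures ANOVA has two error terms. A stable site or PGY effect shifts all three scores of a resident equally. It enters the between-subject error (instruction main effect) and cancels from the within-subject error (instruction by time). This was checked in one simulated dataset of 160 residents. A stable site effect with variance equal to the residual variance at one assessment was added, a deliberately large value. The F for instruction fell from 6.55 to 1.52, and the F for instruction by time stayed at 0.853. A plain group comparison at post-training, which is the named primary outcome, behaves like the first test.

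**3. Size of the gain.** Let f be the share of post-training GRS variance, among what remains after pre-training GRS, that site and PGY explain. The documents give no value, so f is assumed.

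- Standard error ratio = √(1 − f)
- Equivalent number of residents = 160 / (1 − f)
- Power = Φ(2.802 / √(1 − f) − 1.960), starting from the planned 80%

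| f (assumed) | SE ratio | SE cut | Equivalent N | Power |
|---|---|---|---|---|
| 5% | 0.975 | 2.5% | 168 | 82.0% |
| 10% | 0.949 | 5.1% | 178 | 84.0% |
| 20% | 0.894 | 10.6% | 200 | 87.9% |
| 30% | 0.837 | 16.3% | 229 | 91.7% |

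**4. Why f must be counted beyond baseline.** Pre-training GRS absorbs part of the same stable variance. As an illustration with assumed shares, let site and PGY be 20% of variance at both times, other stable skill 30% and noise 50%.

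- The pre-post correlation is 0.50, so baseline alone leaves 1 − 0.50² = 0.75.
- With site and PGY added, the residual is 0.80 × [1 − (0.30/0.80)²] = 0.6875.
- The SE ratio is √(0.6875/0.75) = 0.957, a cut of about 4%.
- So a raw share of 20% becomes f = 1 − 0.6875/0.75 = 8%.

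**5. Direction of the error.** The simulation used 4,000 runs, five sites of 32 with 16 per arm (what 160 residents over five sites requires), and variance split equally between site and PGY. It had no pre-training covariate, so its share is a raw one. The Monte Carlo error on a 5% rate is about 0.3 points.

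| Share | Type I error, unadjusted / adjusted | Power, unadjusted / adjusted |
|---|---|---|
| 0% | 5.2% / 5.2% | 81% / 81% |
| 10% | 4.0% / 4.7% | 79% / 82% |
| 20% | 3.6% / 5.1% | 80% / 86% |
| 30% | 3.3% / 5.1% | 82% / 91% |

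The unadjusted test is conservative, and the adjusted one holds close to its level. The 0% row shows that the extra terms cost almost nothing if they explain nothing.

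**The case against.** **Prior experience may vary little.** The Background says residents are unlikely to have met this technique, and the Discussion argues that its rarity and novelty keep baseline variation small. This stands as a reason to expect the lower end of the range. It does not speak to differences between programmes or to general procedural seniority over five training years.

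**The repeated measures model already handles stable differences.** This is true for instruction by time. It is not true for a post-training comparison or for the instruction main effect.

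**Balance within site is implied, not stated.** Blocking or stratification by site is not spelled out. With simple randomisation at each site, the unadjusted test would keep its nominal level, and only precision would be lost.

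**Covariates may be left to an analysis plan.** The article does not rule them out, and a fuller document may add them. But it does not leave the model open: it names the factors one by one, and that named model is what is questioned here.

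**A stronger reading.** A reader might infer that PGY is the dominant predictor of skill, and that a chance imbalance in seniority would pass as an effect of the teaching method. The documents do not support this. Nothing in them ranks PGY as a predictor, and the remarks on novelty point the other way. Random assignment leaves the unadjusted estimate unbiased, the 5% error rate already allows for chance imbalance, and the simulation shows no excess of false positives.

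**Conclusion.** The point holds as one of efficiency. For the post-training group difference and the instruction main effect, the stated model leaves site and PGY variance in the error. The result is a less precise comparison, and a somewhat conservative test if arms are balanced within site.

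The gain from adjustment is a standard error about 3–16% smaller, for an assumed 5–30% of the variance remaining after pre-training GRS. The lower end is more plausible on the article's own account. These shares are assumptions, and nothing in the document fixes them.

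It does not follow that the trial's standard error is too large overall. Residents train in groups of 4–6 with one instructor. That dependence acts in the opposite, anti-conservative direction, and a site term does not remove it. The net direction is unknown.

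**What to change.** State in the Statistical analysis section that the primary post-training comparison uses a model for post-training GRS with instruction, pre-training GRS, site (fixed, five levels) and PGY level. Report the adjusted difference as primary and the unadjusted difference as a sensitivity analysis. Fix whether PGY enters as linear or categorical before the data are seen.

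The cost is one sentence. Site takes four degrees of freedom and PGY one (linear) to four (categorical), so five to eight out of 160, with one more for pre-training GRS. No new data are needed beyond recording each resident's site and PGY level.

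This change does not deal with the shared-instructor groups, which need their own provision in the analysis.

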#### Deliberate practice and mastery learning

In the DP + ML group, the instructor will demonstrate the procedure following the list of essential steps, published previously [38]. These steps were selected using a modified Delphi methodology. Participants will perform each step under direct instructor observation in keeping with mastery learning techniques [8] and subsequent practice will follow principles of deliberate practice – with the goal of skill improvement using repetitive performance coupled with personalized feedback from the instructor. Chronometry will be introduced in later stages of practice through timed performance [20]. We chose to incorporate chronometry as an additional pedagogic intervention in later stages of learning to further incentivize practice with an objective feedback metric. The training session will be considered complete once the participant and instructor independently agree that competent skill performance is achieved.

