### Sample size determination

A justification of sample size requires knowledge of results from similar studies. As there have been no studies of this exact design conducted previously we have used a sample size formula to evaluate our proposed sample size [40]. We base the sample size calculation on assumptions inherent of a between groups comparison [40]. Given the multi-site nature of this study, there will be approximately 16–20 participants in each site; for a total of 80 in each group. At 80 participants in each group, there is sufficient power (80%) to detect a difference in GRS score of 1.3 between groups, assuming α = 0.05 and β = 0.2 to detect. Similar approaches have been used by Freidman et al. [39] and Naik et al. [41].

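### Residents are trained in groups of 4–6 under one arm-specific instructor, but the stated primary analysis and sample size treat them as independent

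*Protocol article*

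**What the plan says.** Under Instructional methods, the protocol article makes the resident the unit of assignment: "Residents at each study site will be assigned to receive either DP + ML, or self-guided practice using a computer-generated randomization process". Training is then organised in groups: "we will cluster 4–6 participants with 1 instructor who will facilitate the training using one of the two instructional methods". Instructors belong to one arm's session and are briefed differently by arm. For example: "The instructors assigned to the self-guided practice session will be told explicitly that they can only provide feedback following a participant request".

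In the DP + ML arm the instructor demonstrates, watches each step and gives individual feedback. Under Deliberate practice and mastery learning, the session ends "once the participant and instructor independently agree that competent skill performance is achieved". The amount of training thus depends partly on the instructor's own standard.

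Under Primary outcome: "The primary outcome is the difference in skill performance of BAC between the two groups at post-training". Under Sample size determination: "We base the sample size calculation on assumptions inherent of a between groups comparison". The result given there is: "At 80 participants in each group, there is sufficient power (80%) to detect a difference in GRS score of 1.3 between groups". Under Statistical analysis, the GRS score is to be "evaluated using a repeated measures ANOVA with between subject factor of instruction (DP + ML or SG group"), and the only other factor is the assessment occasion (pre, post, retention). None of these sections gives a term or an allowance for training group, instructor or site.

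**The concern.** Residents in one group share a demonstration, a style of feedback and, in DP + ML, a judgement of when training is complete. The primary score is recorded straight after that session. It is plausible that residents trained together score more alike than residents trained apart. Because each group receives only one method, variation between groups feeds directly into the difference between arms. A model with instruction and occasion alone judges that difference against variation between individual residents, which is too small a yardstick if groups differ.

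The trial is meant to tell educators whether a resource-intensive method earns its cost. If the test rejects more often than its nominal 5%, the risk is that a superiority claim for one method partly reflects who taught.

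**Working it through.** **Inputs from the protocol article.** Group size m = 4–6 (Instructional methods); 80 per arm, difference 1.3, 80% power, α = 0.05 (Sample size determination); two-sided test (Statistical analysis).

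**Assumptions.** The ICC is not stated, so 0.01 to 0.20 is shown, with m = 5 as the central case. At 80 per arm there are between 80/6 ≈ 13 and 80/4 = 20 groups per arm, or 80/5 = 16 at m = 5.

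**Step 1: the plan's own figure.** It cannot be reproduced, because no SD is given. Solving backwards, SD = 1.3 / [√(2/80) × (1.960 + 0.842)] = 1.3 / 0.443 = 2.93.

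**Step 2: type I error.** Design effect DE = 1 + (m − 1) × ICC. The unadjusted two-sided test then has type I error 2 × [1 − Φ(1.96/√DE)]. At ICC 0.10 and m = 5, DE = 1 + 4 × 0.10 = 1.40 and 1.96/√1.40 = 1.66, which gives 9.8%.

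That formula is for a simple two-group test, so the stated repeated measures ANOVA was also simulated (4,000 runs, 16 groups of 5 per arm, group effect at post-training and retention only, no site effect). At a true rate near 10%, the simulation error is √(0.10 × 0.90/4000), about half a percentage point.

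| ICC (m = 5) | DE | Formula | Simulated: post-training contrast | Simulated: arm main effect | Simulated: arm-by-time interaction |
|---|---|---|---|---|---|
| 0 | 1.00 | 5.0% | 4.8% | 4.7% | 5.4% |
| 0.01 | 1.04 | 5.5% | not run | not run | not run |
| 0.05 | 1.20 | 7.4% | 7.1% | 6.4% | 6.9% |
| 0.10 | 1.40 | 9.8% | 10.3% | 8.7% | 9.7% |
| 0.20 | 1.80 | 14.4% | 15.5% | 12.1% | 14.3% |

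With clustering in the DP + ML arm only, at ICC 0.10, the three simulated rates were 7.7%, 7.2% and 6.9%. Group size matters less than ICC: by the formula, m = 4 to 6 gives 6.8% to 8.0% at ICC 0.05 and 8.6% to about 11% at ICC 0.10.

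**Step 3: detectable difference.** Taking the plan's 80% for 1.3 as given, the difference detectable with 80% power is 1.3 × √DE. This needs no SD.
- ICC 0.05: 1.3 × √1.20 = 1.42
- ICC 0.10: 1.3 × √1.40 = 1.54

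**The case against.** The strongest reply is that this is an individually randomised trial with small groups, and that the ICC is entirely assumed. The article describes features that could keep it low: every instructor is briefed and taught a standard approach, DP + ML follows a fixed list of steps to an agreed standard, and self-guided instructors respond only when asked. At ICC 0.01 the inflation is trivial, and at zero there is none. This stands as a limit on size. It does not show that the correlation is negligible, and nothing in the article does.

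A second reply is that assignment within site roughly balances site differences between arms. Leaving site out of the model keeps that variation in the error term, which is conservative and may partly offset the inflation. This stands too, and it is why site belongs in the revised model.

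A third is that an article condenses its plan and random effects are often left to an analysis plan. But the article names both the model and the sample size basis, and both assume independent residents. A later plan could repair this only by departing from the stated model.

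A reader might infer more than the article supports:

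- *That the stated 80% power is not delivered.* This cannot be shown. The implied SD of 2.93 is close to the maximum of (7 − 1)/2 = 3 if the GRS is analysed as one score from 1 to 7 (an assumption). With an SD of 1.5 or less, power for 1.3 stays above 97% even at ICC 0.20 and m = 6.
- *That instructor and arm are fully confounded.* With 13–20 groups per arm, variation between groups can be estimated.
- *That one or two outstanding instructors could produce significance alone.* With 16 groups per arm, two instructors each lifting their group by a full SD move the arm mean by 2/16 = 0.125 SD. Against a standard error of √(2/80) = 0.158 SD, that is z ≈ 0.8.
- *That one instructor teaches a whole arm at a site.* The article does not say so, nor whether any instructor leads more than one group. If some do, the effective clusters are larger and the inflation is worse.

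**Conclusion.** The point holds as an error in the stated analysis and in the basis of the sample size. Any positive within-group correlation makes the planned arm comparison anti-conservative, whichever ANOVA term is read as the primary test. For ICCs of 0.05 to 0.10 with 5 per group, the nominal 5% becomes roughly 6–10%.

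These figures assume the same ICC in both arms, one instructor per group and no site effect. In the simulation, the group effect is also absent at baseline. Since baseline is recorded after the session instructor's demonstration, some of it could already be present there; the interaction would then be less affected and the main effect more so.

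Type I error is the firmer consequence. The effect on power can be stated only relative to the plan's unverified 80%.

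**What to change.** 1. Record training-group and instructor identifiers for every resident at the training session, if this is not already planned. They may be hard to reconstruct later.
2. Analyse post-training GRS with a linear mixed model: arm and site as fixed effects, a random intercept for training group (or for instructor, if one instructor leads several groups), and Satterthwaite or Kenward-Roger degrees of freedom.
3. Restate the detectable difference as the unclustered value × √[1 + (m − 1) × ICC], giving the assumed SD, ICC and group size.

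Randomisation, training and recruitment do not change. The cost is two recorded identifiers, revised analysis wording, slightly wider confidence intervals and a slightly less favourable stated detectable difference.
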